### Follow-ups

On the 13^th ^week, each participant undergoes an outcome assessment. After the assessment, the participant will be issued a pedometer (HJ-109 Omron Healthcare, Japan) for daily quantifying of physical activity via number of steps taken for the day [43]. Participants in both groups will continue with the home exercises after the last supervised exercise session. The pedometer is used to gauge and encourage physical activity of the participants. A follow-up monitoring of change on the 24^th ^week will assess changes in self efficacy, impairments, functional changes and quality of life. Monthly from week 14 to 52, the participants will be contacted for any events of fall. The pedometer reading will be correlated with the change in outcome measures from week 13 to 24.

### Sample size

Our primary endpoint is a change in MFES scores immediately post-intervention. There was no literature of MFES investigated in the moderately frail population. We estimated the minimum clinically important difference (MCID) to be detected between the novel intervention programme and the traditional supervised exercise programme and derived a change in 1.5 MFES units. Previous randomised controlled trial showed no change in MFES scores post intervention because healthy volunteers were recruited in their study [25]. The use of healthy volunteers resulted in a ceiling effect in that trial. In the absence of trials assessing MFES in the moderately frail older adults, we assumed a common between-participant standard deviation of 2 units for MFES [25]. This translates to a standardized effect size of interest (Cohen's ***d***) of 0.75. Accordingly, the required sample is 30 participants per group for a two-tailed comparison of the groups when ***d ***is 0.75, power is 0.8 and type I error is 0.05. Considering a 15% drop-out rate, 80 participants will be recruited.

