### Statistical methods

Missing data will be analysed by intention-to-treat approach. Baseline measures for age, body mass index, MFES, TUG test, 6MWT, PPA knee extension strength, NCW test, SF-36v2 and EQ-5D will be analysed for normality. The primary outcome measure is the change in MFES score. Outcome measures will be quantitatively analysed with the mixed model for between group comparisons for statistically significant difference. Statistical significance is set at *p*(2-tailed) < 0.05. Clinical significance will also be analysed based on MCID or minimal detectable change for each of the outcome measures. The mean MCID will be obtained from participants who have a rating of 3 on the GROC scale.

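### The sample size for a change-in-MFES endpoint rests on an SD that reads as a score SD from a ceiling-affected trial, so the 80% power claim depends on an unstated baseline correlation; conditioning on baseline MFES would remove that dependence.

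*Protocol article*

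**What the plan says.** The protocol article defines the endpoint as a change in two places. The Sample size section has "Our primary endpoint is a change in MFES scores immediately post-intervention", and Statistical methods has "The primary outcome measure is the change in MFES score".

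For the calculation, the Sample size section takes a between-group difference of interest ("derived a change in 1.5 MFES units") and then says "we assumed a common between-participant standard deviation of 2 units for MFES", citing reference 25. Dividing 1.5 by 2 gives d = 0.75. With a "two-tailed comparison of the groups" and "power is 0.8 and type I error is 0.05", it arrives at 30 per group, and recruits 80 to allow for 15% drop-out.

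The same paragraph explains why reference 25 found no change in MFES: "The use of healthy volunteers resulted in a ceiling effect in that trial". It also acknowledges that there are no MFES data in moderately frail people.

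Statistical methods names a mixed model for the group comparison. It mentions no baseline term and does not exclude one.

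**The concern.** There are two separate difficulties.

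- **Score or change.** A between-participant SD of a score is not the SD of a within-person change. The two are equal only at one value of the correlation between baseline and week 13, and the article gives no such correlation. If change is compared without adjustment, the stated power holds only when that correlation is high enough.
- **Source of the SD.** The paragraph uses the ceiling effect to set aside the null result of reference 25, but takes its SD from the same trial. A ceiling tends to compress the spread of scores, so the SD may be too small for people selected for moderate frailty and fear of falling.

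At stake is whether the 80% power for the primary endpoint is supported by what is written, and whether the primary comparison uses the baseline MFES to best effect in a trial of 80 people. An unadjusted change comparison also leaves chance baseline imbalance in the estimate, through regression to the mean.

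**Working it through.** **Inputs from the article:** difference 1.5; SD 2; two-sided alpha 0.05; power 0.8; 1:1 allocation (Design); 30 per group; 80 recruited; 15% drop-out. **Assumed, because the article does not give it:** the baseline to week-13 correlation r, with equal SDs at the two time points. All power figures are for the two-sample t-test (noncentral t).

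**1. The stated figure reproduces.** d = 1.5/2 = 0.75. The normal approximation gives 28 per group and the t-test 28.9, so 29. Power at 30 per group is 0.815. The stated 30 is sound for an outcome whose SD is 2.

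**2. Numbers after drop-out.** 80 × 0.85 = 68, or 34 per arm. The minimum to recruit would have been 60/0.85 = 70.6, so 71; recruiting 80 leaves some slack.

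**3. If 2 is the score SD.**
- SD of change = 2 × sqrt(2(1 − r)). This equals 2 only when r = 0.5.
- SD after baseline adjustment = 2 × sqrt(1 − r²). This never exceeds 2.
- Ratio of the variances, adjusted to change: (1 − r²) / (2(1 − r)) = (1 + r)/2, which is 0.75 at r = 0.5.

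| r (assumed) | SD of change | Power, change, 30 per arm | Power, change, 34 per arm | Adjusted SD | Power, adjusted, 30 per arm |
|---|---|---|---|---|---|
| 0.5 | 2.00 | 82% | 86% | 1.73 | 91% |
| 0.4 | 2.19 | 74% | 79% | 1.83 | 88% |
| 0.3 | 2.37 | 67% | 73% | 1.91 | 85% |
| 0.2 | 2.53 | 62% | 67% | 1.96 | 83% |

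At r = 0 the adjusted SD is 2.00 and power at 30 per arm is 81% (0.815). The one degree of freedom spent on the covariate is ignored.

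**4. Correlation needed for 80% power with unadjusted change.** The largest SD that keeps 80% power is 2.04 at 30 per arm and 2.18 at 34 per arm. Solving 2 × sqrt(2(1 − r)) = SD gives r = 1 − (SD/2)²/2:
- 30 per arm: r = 0.48
- 34 per arm: r = 0.41
- 40 per arm (no drop-out): r = 0.30

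**5. If the SD itself is larger.** SDs of 2.5 and 3 are assumptions; the article gives no basis for any particular value. At 30 per arm:

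| Assumed SD | Power, the article's own formula | Power, baseline-adjusted, r = 0.5 |
|---|---|---|
| 2.0 | 82% | 91% |
| 2.5 | 63% | 75% |
| 3.0 | 48% | 59% |

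At SD 2.5, adjustment reaches 80% at 30 per arm only from r of about 0.58. Adjustment therefore removes the mismatch between score and change, but does not make good an SD that is too small.

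**The case against.** The strongest case on the other side has four parts.

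- **The analysis may already condition on baseline.** Statistical methods lists no covariates or contrasts, and an article may leave these to a fuller document. A change outcome does not exclude it either, since change adjusted for baseline gives the same treatment estimate as the week-13 score adjusted for baseline. This stands. A reader might infer that the trial plans an unadjusted comparison of change, but the text does not say so. If baseline is in the model, the correlation condition falls away.
- **The SD of 2 may be an SD of change.** The wording favours a score SD but does not settle it, and reference 25 is not at hand. This also stands as a limit. It would remove the correlation point but not the doubt about a ceiling-affected source.
- **The trial recruits more than 60.** At 34 per arm the required correlation is 0.41, so figures at 30 per arm alone overstate the dependence. This stands, and both are shown.
- **The direction of error in the SD is not proven.** The article says openly that 2 is an assumption made without data in this population, and restricting entry to SPPB 5 to 9 may itself limit the spread. A reader might infer from the ceiling that the SD must exceed 2, but the article does not establish that.

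What none of this answers is that the Sample size section names a change endpoint, sizes it with an SD described as that of the MFES, and does not link the two.

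**Conclusion.** The point holds as a gap in the sample-size justification. If 2 is a score SD and change is compared without adjustment, the stated power needs r of at least 0.48 at the 30 per arm calculated, or about 0.41 at the 34 per arm expected after drop-out; r is not given.

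A reader might go further and conclude that the trial is underpowered, or that its primary analysis is defective. The article supports neither: a correlation of 0.5 or above would preserve the stated power at SD 2, and the mixed model may include baseline. Nor may the SD of 2 be called conservative without qualification. It is conservative as a residual SD only if the true score SD is 2, which is the very value that the ceiling effect puts in doubt.

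Conditioning on baseline MFES is still the better choice whichever reading is right. It is at least as precise as raw change at every r and takes chance baseline imbalance in MFES out of the estimate.

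**What to change.** **Statistical methods:** define the primary analysis as the between-group difference in MFES at week 13, estimated from the mixed model conditional on baseline MFES, either as a covariate or by constraining the baseline means to be equal across arms.

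**Sample size:** state whether the SD of 2 refers to scores or to change. If it is a score SD, say that it serves as an upper bound for the residual SD on condition that the true score SD is 2. Add a short table of power over an SD range such as 2 to 3, labelled as an assumption, with the correlation used for any adjusted figures.

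**Cost:** wording only. Baseline MFES is already collected, and no participants or visits are added. The power shown at larger SDs will look less favourable than 0.8. Adding fall history and SPPB as covariates, or checking the pooled baseline SD blind to arm, is optional and not part of this fix.

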### Randomisation

Block randomisation will be generated by an independent investigator who is not involved in the outcome assessments and interventions and concealed in sealed envelopes marked 1 to 80. Participants will be randomised after completion of the initial assessment independently by an investigator who is not involved in the outcome assessments.

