**Methods:**

This randomised active-control trial is a comparison between the Nintendo WiiActive programme against standard gym-based rehabilitation of the older population. Eighty subjects aged above 60, fallers and non-fallers, will be recruited from the hospital outpatient clinic. The primary outcome measure is the Modified Falls Efficacy Scale and the secondary outcome measures are self-reported falls, quadriceps strength, walking agility, dynamic balance and quality of life assessments.

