## Background

In Singapore, there is an increasing growth of older adults (300,000) and the prevalence of falls is high with a reported incidence of 129000 per year by the Singapore Ministry of Health in 2007. The common consequences of these falls are fractures and soft tissues injuries that may lead to significant disability [1]. Fractures managed in an acute care setting contribute to rising healthcare cost [2-5]. In addition minor trauma and soft tissue injuries lead to activity avoidance and embeds the fear of further falling psychologically [6].

A previous experience of fall may subsequently cause fear in the older person who will then self-restrict mobility or will depend on others for activities of daily living (ADLs) [7]. Fear of falling significantly contributes to functional decline [7] and the health and well-being of the older person [8-10]. In order to quantify the fear of fall, fall efficacy scales have been developed to assess the perceived confidence of the older population [11-13].

Contribution to frailty is a history of sedentary lifestyle in the older population which results in strength and balance impairment [7,14-16]. There are numerous interventions in rehabilitation to modify fall risk and reverse these impairments. There are many research that addressed rehabilitation in the frail population [16-24]; however those that improve fall efficacy significantly are scarce [25]. The Nintendo Wii system has been postulated to be effective in improving functional performance by enhancing flexibility, balance, strength and coordination training [26]. The additional advantage of the Nintendo Wii system is the visual feedback that the participant receives during the training session. This visual feedback aids the participants to improve balance [27], while the game simulation creates a perception that they can perform high level activities.

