## Objectives

### Primary research hypothesis

The Nintendo Wii group intervention is more effective than the gym-based group intervention in improving fall efficacy and self-reported falls in the older adult aged 60 and above.

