### Participants

The participants are patients from the Singapore General Hospital (SGH) Specialist Outpatient Centre Geriatric Medicine department, SGH Lifestyle Improvement Fitness Enhancement Centre Osteoporosis and Bone Metabolism unit, SGH Physiotherapy Falls Clinic and public volunteers. The volunteers are approached to participate in the study within the hospital premises. The screening of eligible participants is done by a medical doctor or a physiotherapist during consultation sessions. The abbreviated mental test is used to screen for cognitive impairment [28], while the Short Physical Performance Battery (SPPB) is used to stratify frailty [29]. The scores from the AMT and SPPB include or exclude participants from the study.

The inclusion criteria of this study:

• Age 60 years old and above

• Community dwelling

• Independent in ambulation (with or without walking stick assist)

• Have fear of falls in daily activities

• Able to commit 12 weeks of supervised intervention

• Score of SPPB from 5 to 9 (moderately frail)

• Speaks or understands English, Mandarin or local dialects

The exclusion criteria of this study:

• Permanent bedbound status

• Disabled in ambulation

• Significant cognitive disorder (AMT score below 7 for 60-74 years old, below 6 for 75 years old and above)

• Untreated medical conditions

• End-stage illness or disease and/or life expectancy less than a year

• Unstable cerebral haemorrhage in the past 3 months

• Fractures in healing phase

• Surgery in the past 3 months, unless with surgeon's approval

• Pulmonary embolism or deep vein thrombosis in the past 3 months

Participants who are eligible and agree to register for our study will be assessed in the SGH Physiotherapy department for baseline measures by an independent outcome assessor.

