### Baseline data

Demographics are obtained via the assessor on the first assessment session. Baseline demographics include age, gender, ethnic group, living status (staying alone or with family), history of falls in the past 12 months, number of medications, height, weight, resting heart rate, resting blood pressure, AMT, SPPB score and Physiological Profile Assessment (PPA) fall risk score.

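### Prior falls are known before allocation but are not used as a stratum: two envelope series would be a cheap improvement, though the single series is not an error

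*Protocol article*

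**What the plan says.** All places are in the Protocol article.

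- **Population.** The abstract (Methods) states: "Eighty subjects aged above 60, fallers and non-fallers, will be recruited from the hospital outpatient clinic". The criteria under Participants contain no fall-history requirement. Recruitment sources there range from a falls clinic to public volunteers.
- **Timing.** Baseline data lists "history of falls in the past 12 months" among the items obtained at the first assessment. The Randomisation section says: "Participants will be randomised after completion of the initial assessment independently by an investigator". Prior falls are therefore known before an envelope is opened.
- **Allocation.** The Randomisation section describes blocks generated by an independent investigator and "concealed in sealed envelopes marked 1 to 80". No stratification factor is named.
- **Relevance of prior falls.** The Background says: "A previous experience of fall may subsequently cause fear in the older person". The primary hypothesis claims superiority "in improving fall efficacy and self-reported falls in the older adult aged 60 and above", and the Health economic evaluation sets a limit on cost per fall prevented.
- **The word stratify.** It appears once, under Participants: "the Short Physical Performance Battery (SPPB) is used to stratify frailty". There the score decides who is included or excluded; it plays no part in allocation.

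**The concern.** The trial mixes two groups that, on its own reasoning, may differ in fear of falling, and that plausibly differ in later falls. Blocks within one series balance the number of participants per arm. They do not balance the number of prior fallers. With about 40 per arm, one arm could receive noticeably more prior fallers, and a difference in falls between arms would then be harder to attribute to the Wii programme. Falls are named in the primary hypothesis and drive the cost per fall prevented, so a reader of the results would ask about this. The factor is already collected in time, so balancing it needs no new data.

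Stratification also has to be settled before allocation. A later analysis plan can add a covariate but cannot create strata.

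**Working it through.** **The plan's own figure.** Sample size gives 30 per group for a difference of 1.5 MFES units, SD 2, two-sided 0.05 and 80% power. The normal approximation is n = 2 × (1.96 + 0.84)² × (2/1.5)² = 27.9, so 28 per group. The exact t calculation gives 29 (power 80.1%), and 30 gives 81.5%. The stated figure is sound, and stratifying does not change it. The document gives no figure for imbalance in prior fallers, so the rest is computed here.

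**Inputs.** 80 participants and 1:1 allocation, so 40 per arm (Design; Sample size). The share of prior fallers is not stated; 25% to 50% is assumed, that is K = 20 to 40 of 80.

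**Step 1: chance imbalance.** Let X be the number of prior fallers in one arm. With allocation unrelated to fall history, X is hypergeometric (80 in total, K fallers, 40 drawn). The arm difference is |X − (K − X)|/40 = |2X − K|/40. Differences of 10, 15 and 20 points correspond to 4, 6 and 8 people.

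| Assumed prior fallers | P(≥10 points) | P(≥15 points) | P(≥20 points) |
|---|---|---|---|
| 20 of 80 (25%) | 0.439 | 0.196 | 0.069 |
| 24 of 80 (30%) | 0.465 | 0.222 | 0.087 |
| 32 of 80 (40%) | 0.494 | 0.254 | 0.110 |
| 40 of 80 (50%) | 0.503 | 0.263 | 0.117 |

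A 60% share gives the same values as 40%. The formula ignores blocking. A simulation of permuted blocks of 4 and of 8 with 40 fallers gave 0.26 for 15 points and 0.12 for 20 points, so blocks alone give no protection here.

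**Step 2: effect on the falls comparison.** Suppose prior fallers fall at r times the rate of the others (r = 2 to 3, assumed) and treatment has no effect.

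- A 60% v 40% split gives (0.6r + 0.4)/(0.4r + 0.6): 1.6/1.4 = 1.14 for r = 2, and 2.2/1.8 = 1.22 for r = 3.
- A 55% v 45% split gives (0.55r + 0.45)/(0.45r + 0.55): 1.55/1.45 = 1.07 for r = 2, and 2.1/1.9 = 1.11 for r = 3.

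Both examples assume 50% prior fallers overall. The first is a difference of 20 points, and one of at least that size has probability about 0.12, counting both directions.

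**Step 3: effect on MFES.** If prior fallers and non-fallers differ by 0.5 to 2 MFES units (assumed), a 20-point imbalance shifts the unadjusted arm difference by 0.20 × 0.5 = 0.1 to 0.20 × 2 = 0.4 units. Against the 1.5-unit target that is 0.1/1.5 = 7% to 0.4/1.5 = 27%. This is an upper picture, because analysing change from baseline removes part of such a gap.

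**The case against.** The strongest reply is that nothing is wrong. Block randomisation by an independent investigator with numbered sealed envelopes is an accepted procedure for 80 participants, and the protocol never promises stratification. **This stands**, and it is why the point is offered as an improvement.

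Several stronger readings are tempting but are not supported:

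- **That the comparison is biased.** Randomisation is unbiased in expectation and the type I error is kept. Chance imbalance can favour either arm and is already reflected in the standard error. What remains is possible chance confounding in the one allocation that is realised, and some lost precision.
- **That a material imbalance is likely.** A gap of 10 points is about an even chance. One of 15 points is about 1 in 4 to 1 in 5, and one of 20 points about 1 in 8 to 1 in 14.
- **That prior falls are the main prognostic factor.** The Background says only that a previous fall may cause fear. It does not rank fall history above frailty, age or fall-risk score, and it does not say that prior falls predict later ones.
- **That the MFES result is in doubt.** Every participant must already fear falling and score 5 to 9 on the SPPB, which narrows the contrast between fallers and non-fallers. The endpoint is change in MFES, with a baseline measurement.
- **That the SPPB wording promises stratified allocation.** In context it describes screening.

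Three further replies have some force. Falls are secondary in the abstract, and the trial is sized on MFES, although the primary hypothesis names both. The absence of a stratification factor is inferred from the single numbered series in a short article; that inference is reasonable, but the text does not say so outright. Finally, covariates are commonly left to the statistical analysis plan, so the lack of a prior-falls term in Statistical methods is not itself a fault.

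**Conclusion.** The point holds as a low-cost improvement to a valid design. Fallers and non-fallers are both enrolled, fall history is known before allocation, and the described scheme does not use it. An arm difference of 10 points or more in prior fallers is about an even chance, and one of 20 points or more is roughly a 1-in-10 event. An imbalance of 20 points could produce an apparent rate ratio of 1.14 to 1.22 for falls with no treatment effect. The consequence is mainly for the precision and credibility of the falls comparison and the cost per fall prevented; change in MFES is affected less.

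The faller share, the 2- to 3-fold rate and the MFES gap are all assumptions, because the document gives none of them. The facts about enrolment, timing and the single series are in the text.

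**What to change.** **Before allocation starts.** The same independent investigator prepares two separately numbered envelope series, each in blocks: one for participants with at least one fall in the past 12 months and one for those with none. The envelope is drawn from the matching series after the baseline assessment. Each series should be longer than its expected need, since stratum sizes are unknown, with recruitment still stopping at 80. The stratum (yes/no) then enters both the falls model and the MFES mixed model.

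**If allocation has begun.** The Time-line has recruitment starting in July 2010. In that case keep the existing list and prespecify falls in the past 12 months (yes/no) as a covariate before outcome data are examined by arm. This matters chiefly for the falls analysis.

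**Cost.** A second envelope series and one model term, with no extra participants or data. Incomplete last blocks may leave the arms a few participants apart. With blocks of 4 (assumed), each stratum can end at most 2 apart, so the arms can differ by at most 2 + 2 = 4. The excess of prior fallers in one arm would be at most 2, about 2/40 = 5 points.
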